### Therapist

Both studies anticipate the participation of the psychologist and researcher in this study. She is currently the only professional with completed training in both mindfulness strategies through the Mindfulness-Based Health Promotion (MBHP) protocol from the Open Mind Center at the Federal University of São Paulo and in Trial-Based Cognitive Therapy, as developed by [name] [13].

### Results

In Phase 1, encompassing a pilot study, the acceptability of M-TBCT will assess participants’ perceptions regarding satisfaction with the M-TBCT protocol through a self-report questionnaire. The feasibility of M-TBCT will be verified by recruitment rates (>80 %), session attendance (>60 %), and sample retention at the end of the study (>60 %).

In Phase 2, involving the efficacy of M-TBCT, the primary outcome will be assessed by the increase in well-being, measured through WHO-5. Secondary outcomes include a reduction in depression symptoms (PHQ-9), anxiety (GAD-7), cognitive distortions (CD-QUEST) and an increase in self-care capacity (ASAS-R). All scales will be administered in both groups (M-TBCT and waitlist) before the intervention (baseline assessment), at the end of the 8 sessions (final assessment), and at the 6-month follow-up. Table 2 illustrates the session and assessment flow throughout the study period.

**Table 2 tbl0002:** Session and assessment flow throughout the study period.

Study period				
	Enrollment	Allocation	Post-intervention	Follow-up
**Point in time**	Screening	Baseline	8 weeks	6 months

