This research seeks to contribute to the development of targeted interventions that foster a healthier and more resilient judiciary workforce, potentially informing future occupational health initiatives. The primary objectives are to refine the M-TBCT protocol, assess its acceptability and feasibility within the judiciary, and compare its efficacy against a waitlist control group, measuring its impact on key mental health outcomes such as depression, anxiety, cognitive distortions and self-care.

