### Evaluation measures

Assessments will occur pre-intervention (T0), post-intervention (T1), and at a six-month follow-up. These will include questionnaires measuring well-being (WHO-5), depression (PHQ-9), anxiety (GAD-7), reduction in cognitive distortions (CD-QUEST) and self-care (ASAS-R). Post-study, M-TBCT will be offered to the waitlist group if results are favorable. The study stages will follow the CONSORT flowchart [24] depicted in Fig. 1. The study was approved by the Research Ethics Committee of the Federal University of São Paulo (CAAE 73817423.3.0000.5505) and registered in the Brazilian Clinical Trials Registry (REBEC) 〈https://ensaiosclinicos.gov.br/〉.

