### Sample size (Phases 1 and 2)

The sample will consist of magistrates and public servants from the judiciary who score a minimum of 7 points on the recruitment instrument (SRQ-20), which is available for online completion throughout the regional jurisdiction via an electronic platform integrated into TRT5’s intranet.

The sample size for Phase 1 of the study was determined with Soler et al. [23] as a reference, considering a minimum of 30 participants. For Phase 2, the study primarily referred to a meta-analysis conducted by Khoury et al. [39], which assessed the effectiveness of 8-week mindfulness-based interventions in healthy individuals and found an average dropout rate of 10 %.

To establish statistical significance, a sample size of 72 individuals was estimated using G*Power 3.1.9.2, based on a one-tailed *t*-test for independent samples with α=0.05, β=0.20, and Cohen's *d* = 0.6. Considering an approximate dropout rate of 25 %, which is higher than that found in similar studies, an estimated recruitment of approximately 90 eligible individuals for the intervention and control groups is anticipated.

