Randomization success will be determined by no significant differences between the groups regarding demographic and clinical characteristics. Continuous variables will be analyzed using Student's *t*-test, and categorical variables will be analyzed using chi-square or Fisher's exact tests. Longitudinal data (T0, T1, and T2) for both intervention and passive control (waitlist) groups will be tracked using the repeated measures Student's *t*-test. Spearman's correlation test will assess variable correlations. M-TBCT program efficacy will be evaluated using repeated measures ANOVA to examine the main effects of time and treatment and their interaction. McNemar's test will assess changes in mental disorder risk classification after M-TBCT intervention. Effect sizes (Cohen's d) and 95 % CI will be calculated for intra- and inter-group comparisons (intervention and waitlist). The Bonferroni correction will be applied to adjust for various statistical tests.

The data will be analyzed through intention-to-treat (ITT), including all randomized participants in their initially assigned group, regardless of completing the treatment protocol. Per-protocol analysis will exclude participants with fewer than four sessions (50 % of the M-TBCT program). Attrition analysis (As-treated) will compare those who completed the protocol with those who responded only to the initial questionnaire. This study employs mixed-effects linear models (MLMs) for statistical analysis. Fixed variables, including depression, anxiety, and self-care, will be incorporated, whereas random variables will be introduced to capture intra-individual variation over time. This will enable modeling of unexplained individual differences not accounted for by the fixed variables, providing a robust approach to understanding the relationships between these variables and well-being throughout the study.

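### No visit or contrast is named as deciding for WHO-5, and the stated repeated measures ANOVA does not by itself test the end-of-treatment difference on which the trial is sized

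*Protocol article*

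**What the plan says.** Under Results, the Phase 2 "the primary outcome will be assessed by the increase in well-being, measured through WHO-5". All scales are given in both arms "before the intervention (baseline assessment), at the end of the 8 sessions (final assessment), and at the 6-month follow-up". Evaluation measures and Table 2 repeat this schedule, and none of these places marks one visit as primary.

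Under Hypotheses, H2 claims improvement over the control group and gives no time. H3 claims that the benefit is maintained at six months.

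Under Statistical methods: "M-TBCT program efficacy will be evaluated using repeated measures ANOVA to examine the main effects of time and treatment and their interaction". No term or contrast is singled out. The sentence before the ANOVA in the same paragraph describes the longitudinal data as T0, T1 and T2.

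Under Sample size, "a sample size of 72 individuals was estimated using G*Power 3.1.9.2", from a one-tailed independent-samples t-test with α = 0.05, β = 0.20 and d = 0.6. That is one comparison between arms at one unstated time.

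**The concern.** The sizing test and the efficacy test answer different questions. The first compares two arms once. The second offers a treatment main effect averaged over visits and an omnibus group-by-time interaction, besides a time effect that says nothing about the arms. As nobody has said which decides, more than one term and more than one visit could be put forward as the efficacy result once the data are known.

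The terms also have different faults as a test of H2. Randomisation makes the expected baseline difference zero, so a main effect that includes T0 is pulled towards zero. The interaction escapes this, but it has 2 degrees of freedom and mixes the efficacy question (H2) with the maintenance question (H3). A true benefit at the end of treatment could be missed on the main effect. A significant interaction could be reported as efficacy when the arms do not differ at T1.

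**Working it through.** **Inputs from the protocol.** d = 0.6, α = 0.05 one-tailed, power 0.80, 72 evaluable participants allocated 1:1, so n = 36 per arm (Sample size; Randomization and blinding). Visits T0, T1 and T2 (Evaluation measures; Table 2).

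**Assumptions not in the documents.** SD of 1 at each visit, compound symmetry, within-person correlation ρ = 0.3, 0.5 or 0.7, no missing data. True differences between arms are written (T0, T1, T2) in SD units.

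**1. The plan's own figure.** The noncentral t solution is 35.04 per arm, rounded up to 36, or 72 in all. With n = 36 the noncentrality is 0.6/√(2/36) = 2.55 on 70 df, and power is 0.81 one-tailed (0.71 two-sided). The stated 72 is reproduced.

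**2. Treatment main effect.** The estimate is the mean of the three differences. Its variance factor is v = (1 + 2ρ)/3, and the noncentrality is mean/√(2v/n) on 70 df. For (0, 0.6, 0.6) the mean is 1.2/3 = 0.4 SD. At ρ = 0.5, v = 0.667 and the noncentrality is 0.4/√(0.667 × 2/36) = 2.08.

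| True differences | Test | ρ = 0.3 | ρ = 0.5 | ρ = 0.7 |
|---|---|---|---|---|
| (0, 0.6, 0.6) | two-sided | 0.63 | 0.54 | 0.46 |
| (0, 0.6, 0.6) | one-tailed | 0.74 | 0.66 | 0.59 |
| (0, 0.6, 0.3) | two-sided | 0.40 | 0.34 | 0.29 |
| (0, 0.6, 0) | two-sided | 0.21 | 0.18 | 0.15 |

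Every entry is below the planned 0.80, including those on the plan's own one-tailed basis.

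**3. Interaction.** The test is F on 2 and 140 df, with λ = (n/2) × S/(1 − ρ), where S is the sum of squared deviations of the three differences from their mean. For (0, 0.6, 0.6), S = 0.4² + 0.2² + 0.2² = 0.24. For (0, 0.6, 0) and for (0, 0, 0.6), S = 0.2² + 0.4² + 0.2² = 0.24 as well. At ρ = 0.5, λ = 18 × 0.24/0.5 = 8.64.

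| True differences | ρ = 0.3 | ρ = 0.5 | ρ = 0.7 |
|---|---|---|---|
| (0, 0.6, 0.6), (0, 0.6, 0), (0, 0, 0.6) | 0.59 | 0.74 | 0.93 |
| (0, −0.6, −0.6) | 0.59 | 0.74 | 0.93 |
| (0, 0.6, 0.3) | 0.46 | 0.61 | 0.84 |

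Where S = 0.24, power passes 0.80 at a correlation of about 0.57. The test gives the same power for an effect only at T1, an effect only at six months, a sustained benefit and a sustained harm. In a simulation of 10,000 trials per scenario under (0, 0, 0.6), about 98% of the significant interactions came with no significant benefit at T1.

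**4. One named contrast.** For the T1 difference adjusted for baseline WHO-5, the noncentrality is 0.6/√((1 − ρ²) × 2/36) on 69 df. At ρ = 0.5 this is 0.6/√(0.75 × 2/36) = 2.94. Two-sided power is 0.75, 0.83 and 0.94 for ρ = 0.3, 0.5 and 0.7, whatever happens at T2. That is above both ANOVA terms in every scenario tabulated, though at ρ = 0.7 the margin over the interaction is only 0.94 against 0.93.

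**The case against.** The best defence is that T1 is already implied. H2 and H3 read together put efficacy at the end of treatment and maintenance at six months, and Results calls the visit after the 8 sessions the final assessment. That is the sensible reading, and the fix adopts it. But no sentence states it, and if T1 is meant, neither ANOVA term isolates it.

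A second defence is that an outcome worded as an increase points to the interaction, which baseline does not dilute. This is fair, and it limits the main-effect figures to a term that the plan lists but never calls decisive. The interaction still lacks direction and still mixes T1 with T2. Other planned analyses, such as between-group Cohen's d with confidence intervals and mixed models, do not settle the matter, because none is tied to a primary visit.

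Third, T0, T1 and T2 are attached literally to the repeated measures t-test. Three levels for the ANOVA is an inference, but the natural one.

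A reader might also infer more than the documents support:

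- *That neither ANOVA term reaches the planned power.* This holds for the main effect across the range examined. For a sustained effect it fails for the interaction above a correlation of about 0.57. Setting the interaction's 0.74 against 0.81 also compares a non-directional test with a one-tailed one; the two-sided t-test at T1 has 0.71.
- *That a significant interaction can reflect no benefit after treatment at all.* The six-month-only case is still a benefit after treatment. What is absent is a benefit at T1.
- *That the Background leaves the primary outcome in doubt by "measuring its impact on key mental health outcomes such as depression, anxiety, cognitive distortions and self-care".* This is introductory prose with an open-ended list. Results, Instruments and Statistical methods consistently treat WHO-5 as primary.

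**Conclusion.** The point stands in a limited form. The primary outcome is clear, but its deciding visit and contrast are implied rather than stated, and the test fixed for efficacy differs from the one used for sizing. For a benefit of 0.6 SD held from T1 to T2, the treatment main effect estimates two thirds of it and has power of 0.46 to 0.63 two-sided (0.59 to 0.74 one-tailed). The interaction may be well powered or not, depending on the correlation, but a significant result does not by itself establish H2.

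The powers depend on the assumed correlation, compound symmetry and 36 evaluable participants per arm. Two conclusions do not depend on the particular correlation: including T0 reduces the main-effect estimate from 0.6 to 0.4 SD, and under compound symmetry the interaction has equal power for an effect only at T1 and an equal effect only at six months. The deciding visit and contrast are core protocol content, and the article does not leave the test open, so this is more than detail awaiting an analysis plan.

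**What to change.** State that the single primary test is the M-TBCT minus waitlist difference in WHO-5 at T1 (8 weeks), adjusted for baseline WHO-5, by ANCOVA or the matching mixed-model contrast. Make the difference at T2 a named secondary test for H3. Attach T1 to H2, and tie the sample size to the T1 contrast. The ANOVA need not be removed: its treatment main effect and omnibus interaction can stay as supportive analyses.

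The cost is wording in the outcome, hypothesis, sample size and analysis sections, with no new data. The small downside is that a benefit appearing only at six months would not count as the primary result.

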**Recruitment**				
SRQ-20	X			
Eligibility	X			
Informed consent		X		
Allocation		X		
**Intervention (M-TBCT)**				
**Control group (waiting list)**				
**Assessments**				
**Phase 1**				
Self-report questionnaire			X	
**Phase 2**				
WHO-5		X	X	X
PHQ-9		X	X	X
GAD-7		X	X	X
CD-QUEST		X	X	X
ASAS-R		X	X	X

### Instruments

•Recruitment (Phases 1 and 2)

*Self-Report Questionnaire (SRQ-20):* This self-administered questionnaire, originally developed by the World Health Organization and validated for use in Brazil [28], serves as a screening tool for common mental disorders in Brazilian studies, particularly among worker groups [29]. Comprising 20 "yes" or "no" questions related to symptoms of common mental disorders, a cutoff point of 7 indicates a classification of suspected cases. The validated version for use in Brazil will be employed.

It will also involve the utilization of a self-report questionnaire, enabling individuals to disclose the following non-inclusion criteria: (1) the presence of severe symptoms indicative of an ongoing mental disorder or organic disease; (2) the presence of a personality disorder, a diagnosis of schizophrenia, psychotic disorder, suicidal ideation, or the use of substances causing cognitive impairment affecting attention and concentration; (3) being in the initial phase or undergoing adaptation to pharmacological and/or psychotherapeutic interventions; (4) maintaining regular engagement in mindfulness, meditation, or analogous practices.•Acceptability and feasibility (phase 1)

Acceptability assesses participants’ perceptions of satisfaction with the M-TBCT protocol. All participants who complete the eight sessions of the program will be invited to complete a self-report questionnaire asynchronously, individually, and online within one week after the intervention. The questionnaire consists of two parts. The first part contains 6 items scored from 0 to 4, where 0 = completely dissatisfied and 4 = completely satisfied, covering the following topics: (1) motivation to participate in the program; (2) therapist's competence; (3) online modality of the intervention; (4) session duration; (5) weekly interval between sessions; (6) quantity and quality of services offered (intervention and support materials); (7) utility of the program in resolving and/or dealing with problems; (8) if the program met expectations; (9) if they would recommend the intervention to others; (10) if they would use the program again; (11) if the program contributed to adhering to what was learned, and (12) overall satisfaction with the program. This part of the questionnaire was adapted from Loucks et al. [30] and Martínez-Sanchis et al. [31]. According to these authors, an intervention is considered well-received when most assessed aspects are recognized by participants as appropriate.

The second part of the questionnaire was adapted from Soler et al. [23], including structured questions about the acceptability and feasibility of the M-TBCT protocol, aiming to cover: (1) the respondent's understanding of well-being and self-care; (2) verifying if and how the protocol contributed to the promotion of well-being and self-care in their daily lives; (3) identifying the practices learned in the protocol that most contributed to the promotion of well-being and self-care in daily life; (4) verifying if there were any challenges that the participant encountered in adhering to the protocol sessions and including practices in daily life; and (5) identifying if there were any practices learned in the protocol that were easier to include in daily life.

According to the literature, the feasibility of an intervention requires meeting at least three of the following indicators: (1) recruitment rate greater than 80 % of the sample size; (2) retention rate equal to or greater than 60 % measured by participation in the final follow-up assessment; (3) attendance rate equal to or greater than 60 % of the total sessions; and (4) intervention evaluation [32].

Previous studies have found good acceptability and feasibility of mindfulness-based interventions, for example, for the self-regulation of blood pressure in hypertensive patients [30]. However, until now, no studies have been identified that verify the acceptability and feasibility of a mindfulness and a TBCT protocol for the main outcome proposed to be measured in this study (psychological well-being), neither with reference to the judiciary.•Primary Outcome (Phase 2)

The World Health Organization Five (WHO-5) is a concise, self-administered scale developed by the WHO to evaluate subjective well-being. It is widely used as an outcome measure in clinical trials and has undergone various validity studies for use in Brazil. When applied in clinical trials, the WHO-5 effectively captures improvements in well-being resulting from both pharmacological and non-pharmacological interventions across diverse conditions and contexts [33]. The scale comprises five questions organized in a Likert-type scale ranging from 5 (all the time) to 0 (never). Raw scores range from 0 (absence of well-being) to 25 (maximum well-being). It is recommended to multiply the raw score by 4, yielding a scale from 0 (absence of well-being) to 100 (maximum well-being). According to the WHO guidelines, a cutoff score of 50 indicates screening for clinical depression [33].•Secondary Outcomes (Phase 2)

The Patient Health Questionnaire-9 (PHQ-9) serves as a self-report tool for the brief assessment, diagnosis, and monitoring of depression, aligning with the DSM-IV criteria and reflecting experiences over the past two weeks. Comprising nine items, the questionnaire uses a Likert-type scale with four points ranging from 0 (not at all) to 3 (nearly every day) . A cutoff score of 10 indicates the presence of signs and symptoms of major depression [34]. We will use the validated version tailored for use in Brazil.

The Generalized Anxiety Disorder-7 (GAD-7) serves as a self-report instrument for the concise assessment, diagnosis, and monitoring of anxiety, aligning with the DSM-IV criteria and encompassing the preceding two weeks. Developed by Spitzer et al. [35], consisting of seven items, the questionnaire employs a Likert-type scale with four points ranging from 0 (not at all) to 3 (nearly every day). A cutoff score of 10 indicates the presence of signs and symptoms of generalized anxiety disorder [34]. We will use the validated version designed for Brazil.

The Cognitive Distortions Questionnaire – 9 items (CD-QUEST-9) this is a brief self-report 9-item version [36] of the original 30-item tool developed and validated by [name] et al. [37]. The short version consists of nine cognitive distortions, evaluated in terms of intensity and frequency of occurrence in the last week when completing the questionnaire. The frequency-intensity cross-classification for each of the 9 cognitive distortions includes frequency options such as “No (It did not occur),” “Occasional (1–2 days during the past week),” “Much of the time (3–5 days during the past week),” and “Almost all the time (6–7 days during the past week).” Intensity options include “A little (Up to 30 %),” “Much (31–70 %),” and “Very much (>70 %).”

The Revised Self-Care Assessment Scale (ASAS-R) [38] assesses the levels of health-related self-care capacity within the Brazilian population. It focuses on health-promoting behaviors developed over the course of one's life, not solely when health issues arise. The scale consists of 15 items evaluated using a Likert-type scale ranging from 1 (strongly disagree) to 5 (strongly agree). It demonstrates a good fit and reliability with the three-factor model of the original scale, namely: Factor 1: Having the capacity for self-care (items 1, 2, 3, 5, 6, and 10); Factor 2: Developing the capacity for self-care (items 7, 8, 9, 12, and 13); and Factor 3: Lack of capacity for self-care (items 4, 11, 14, and 15). Damásio and Koller [38] validated its use in Brazil.

The outcome measures will be administered in an online, individual, and asynchronous format, applied before the intervention (T0), after the intervention (T1), and at the 6-month follow-up.

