## Description of protocol

### Study design

This study consists of two phases. The first is a pilot study to develop the M-TBCT protocol, assessing its suitability and practicality within the judicial context. The second phase is an efficacy trial using a single-blind design with two groups: an M-TBCT intervention group and a waitlist control group. Inspired by Soler et al. [23], the first phase will involve a sample of 30 participants, divided into three blocks of 10, each receiving M-TBCT in eight weekly one-hour sessions. Participant feedback via a self-report questionnaire will guide protocol refinement.

The second phase, an efficacy trial, will have 90 participants randomly assigned to either the intervention or waitlist group, each receiving the same M-TBCT regimen. The M-TBCT protocol will be administered individually on a weekly basis, with each session lasting 1 h and totaling 8 online sessions.

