### Hypotheses

Based on prior research, we hypothesize:

Hypothesis 1 (H1)M-TBCT will demonstrate acceptance and feasibility among judges and public servants in the judiciary.

Hypothesis 2 (H2)M-TBCT will significantly improve psychological well-being, self-care, and reduce anxiety, depression and cognitive distortions compared to the control group.

Hypothesis 3 (H3)The benefits of M-TBCT will be maintained at the six-month follow-up.

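### Phase 1 acceptability is asked only of participants who complete all eight sessions, so the result leans favourable; the questionnaire's item count also needs reconciling

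*Protocol article*

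**What the plan says.** The Instruments section fixes who receives the acceptability questionnaire: "All participants who complete the eight sessions of the program will be invited to complete a self-report questionnaire". It is filled in online within a week of the end of the intervention.

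The Results section makes this the acceptability measure: "the acceptability of M-TBCT will assess participants’ perceptions regarding satisfaction with the M-TBCT protocol through a self-report questionnaire". The hypothesis it serves is H1: "M-TBCT will demonstrate acceptance and feasibility among judges and public servants in the judiciary". Under Study design, "the first phase will involve a sample of 30 participants, divided into three blocks of 10", and participant feedback by questionnaire is to guide refinement of the protocol.

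Part two of the questionnaire includes an item on "verifying if there were any challenges that the participant encountered in adhering to the protocol sessions". Part one is introduced with "The first part contains 6 items scored from 0 to 4", but the numbered list that follows runs to "12) overall satisfaction with the program". The criterion, attributed to cited sources, is that "an intervention is considered well-received when most assessed aspects are recognized by participants as appropriate".

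**The concern.** Acceptability is judged only by those who stayed to the end. People who disliked the online format, the session length or the weekly interval are more likely to leave, and leaving removes their rating. The selection works in one direction: the more the intervention puts people off, the fewer of those people are heard.

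Two uses are affected. One is the acceptance half of H1. The other is the feedback meant to improve M-TBCT before Phase 2, which would lack the accounts of those who found it hardest to continue. The item on obstacles to attending sessions is the clearest case, since it goes only to people who completed the sessions.

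The item count is a smaller matter. The criterion speaks of most aspects, and the document leaves open whether there are six or twelve.

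**Working it through.** **Who is asked, and whether anything else fills the gap.** On a strict reading of Instruments, a participant who misses one session is not invited. On a looser reading (reached the end of the programme), only those who stop are left out. Either way, leavers are not asked. The other Phase 1 sources are:

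- Recruitment, attendance and retention (Results, Instruments): attendance and retention reflect people who leave, but record no opinions.
- The analysis of characteristics that raise or lower adherence (Statistical methods): it can show who adheres less, but not why, or what they thought of the format.
- No exit form or other acceptability data from leavers is described.

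**How much the restriction could matter.** Inputs: N = 30 enrolled (Study design). The number of completers m and the number of satisfied completers s are assumptions, because the document gives no expected rate of completing all eight sessions. Every completer is assumed to respond, and all 30 to have started. Then:

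- Satisfaction among completers = s / m
- Lower bound over all enrolled (no leaver satisfied) = s / N
- Upper bound over all enrolled (every leaver satisfied) = (s + N − m) / N
- Width of the interval = (N − m) / N

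| Completers m | Satisfied s | Among completers | Lower bound | Upper bound | Width |
|---|---|---|---|---|---|
| 27 | 24 | 24/27 = 89% | 24/30 = 80% | 27/30 = 90% | 3/30 = 10 points |
| 24 | 20 | 20/24 = 83% | 20/30 = 67% | 26/30 = 87% | 6/30 = 20 points |
| 22 | 20 | 20/22 = 91% | 20/30 = 67% | 28/30 = 93% | 8/30 = 27 points |
| 18 | 15 | 15/18 = 83% | 15/30 = 50% | 27/30 = 90% | 12/30 = 40 points |

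The rows with 27 and 22 completers roughly match the 10% and 25% dropout figures in the Sample size section, which were given for Phase 2. The width depends only on how many leave. In each row the completer figure lies inside the interval and nearer its upper end.

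**Item count.** The stated number is 6. The topics are numbered (1) to (12), so the count is 12 and the stated figure does not reproduce. If most is taken to mean more than half, the threshold would be at least 4 of 6 or at least 7 of 12. Six items covering twelve topics is conceivable but unlikely, since each item carries a single 0 to 4 rating and the topics are distinct.

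**The case against.** The strongest reply is that Phase 1 is a descriptive pilot. Statistical methods says its quantitative analysis is mainly descriptive and that satisfaction and feedback are grouped qualitatively into themes. Completers can still rate the session length or format poorly, and someone who attended one session cannot sensibly rate several of the topics. All of this is fair. It limits the consequence and shapes the remedy, but it does not supply the missing views.

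Several stronger readings are tempting, and the document does not support them:

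- A reader might infer that the plan will report a percentage satisfied. It defines no such endpoint. The criterion counts aspects, not people, so the percentages above only illustrate the selection.
- A reader might take the 60% thresholds to mean that 18 of 30 are expected to finish. They concern participation in the follow-up assessment and the share of sessions attended, not completion of all eight. Eighteen is an assumption.
- A reader might show only the case in which every leaver is dissatisfied. That is a lower bound; the upper bound belongs beside it.
- A reader might infer that a feasibility indicator is compromised. The fourth indicator, evaluation of the intervention, is not equated with this questionnaire. Results judges feasibility by recruitment, attendance and retention alone, and Instruments requires only three of the four indicators.
- A reader might call a favourable result close to automatic. The text shows a bias in that direction, not a foregone result.
- A reader might conclude that the count must be 12, the score range 0 to 48 and the rule 7 of 12. The instrument is not shown and no summed score is used, so the document supports reconciliation only.

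**Conclusion.** The point holds in a limited form. As written, the acceptability result describes completers only, and so is biased toward a favourable view of M-TBCT, as is the feedback used to refine it. The direction rests on the reasonable assumption that people who leave are on average less satisfied than those who stay. The size cannot be determined from the document: under the assumed scenarios, the figure for all 30 is uncertain by 10 to 40 percentage points. The issue is confined to Phase 1 acceptability and refinement; it does not touch H2 or H3. It is a worthwhile, low-cost improvement. The mismatch between six items and twelve topics is a genuine but minor contradiction.

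**What to change.** - Invite every Phase 1 participant who attended at least one session to complete the existing online form, or those of its items that apply, at the end of the programme or within one week of stopping. Keep the item on obstacles to attendance for all of them.
- Report acceptability for all who started, with the number of non-responders shown, and give the completer result alongside.
- Check the stated 6 items against the actual instrument and correct either the number or the list, so that the rule about most aspects has a fixed denominator.

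The cost is a few additional online invitations, with no new instrument. The response rate among leavers will be lower, and they will be unable to rate some items; showing non-responders and item-level denominators makes both visible. The change is needed before Phase 1 feedback is used to refine the protocol.
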